#### Exploratory outcomes

Explore host-derived diagnostic markers and markers that predict the clinical outcome by protein and transcriptional profiling assays (collected at defined time points (Fig. 2) during the hospital stay)Compare evaluation of sputum quality when judged by traditional microscopic criteria (performed as part of standard of care by clinical microbiologists at the laboratory) versus pre-specified macroscopic criteria for manual inspection (by the sputum collecting personnel in the emergency department)Explore the aetiology and hospital management of CAP in relation to earlier exposure to antibiotics, vaccination, comorbidity, medication, smoking status, alcohol use, travelling history, hospitalization and frailty indicators including nursing home residency and scoring systems (clinical frailty scale)

Furthermore, several additional outcomes will be used to explore timings of the individual parts of the interventions:

A.Time (in minutes) used for obtaining a lower respiratory tract sample (time from start to stop of the induced sputum/endotracheal aspiration procedure)B.Time used from admission to time of:Inclusion (in minutes)Obtaining induced sputum/tracheal aspirate (in minutes)Sampling throat swab for SARS-CoV-2 (in minutes)Randomised (in minutes)A microbiological test result obtained from the sputum sample (time of the sputum culture report and/or time of the FAP *plus* result) (in hours)

### Participant timeline {13}

The participant timeline is shown in Fig. 1. A schematic diagram with the time schedules for enrolment, interventions and assessments for participants is shown in Fig. 2. Eligible patients are identified and included in the emergency department. Due to local infection control regulations, the patient’s SARS-CoV-2 status is clarified before collection of lower respiratory tract samples. Following consent, all suspected CAP patients are tested for SARS-CoV-2 by naso- and oropharyngeal swab samples. In both SARS-CoV-2- negative and SARS-CoV-2-positive patients, collection of lower respiratory tract samples is performed as soon as possible in the emergency department, either by induced sputum or by endotracheal aspiration. Spontaneous sputum is collected as an exception if an induced sputum cannot be collected. If sputum induction is unsuccessful, endotracheal aspiration is performed. Respiratory tract samples are sent immediately via a pipeline system to the Department of Microbiology at HUH, where microbiological testing takes place. In patients randomised to the FAP *plus*, the test result is phoned to the treating staff.

**Fig. 1 Fig1:**
[figure not shown]
Participant timeline. Overview of the participant timeline. *Abbreviations:* ED, emergency department; FAP *plus*, BioFire® FilmArray® Pneumonia Panel *plus* (bioMérieux S.A., Marcy-l’Etoile, France); PCR, polymerase chain reaction

**Fig. 2 Fig2:**
[figure not shown]
Schedule of enrolment, interventions and assessments. ^a^At discharge or on day 3, whichever comes first. ^b^Day 30. ^c^Post-discharge at day 30, day 90, 1 year and 5 years. *Abbreviations:* ED, emergency department; FAP *plus*, BioFire® FilmArray® Pneumonia Panel *plus* (bioMérieux S.A., Marcy-l’Etoile, France)

Blood samples for standard biochemistry and cultures, urine for antigen testing (*Streptococcus pneumoniae*) and clinical data collection including scoring systems and physical tests are performed at the emergency department. Furthermore, at admission and on day 3, blood ethylenediamine tetra-acetic acid- (EDTA) and PAXgene blood RNA tubes (PreAnalytiX, Hombrechtikon, Switzerland) are collected and subsequently frozen in a biobank at HUH.

### Sample size {14}

To ensure a sufficiently large sample size to address the multiplicity issue introduced by considering two primary outcomes, we take a slightly conservative approach of assuming that the two outcomes are uncorrelated, implying that separate sample size calculations for the two outcomes must be carried out at a significance level of 0.025 instead of 0.05.

In a prospective study on hospitalized CAP patients, with stringent inclusion criteria (that included the presence of a new pulmonary infiltrate on chest radiograph), we showed that microbial aetiology with a combination of molecular and conventional methods could be established in 63% of included patients [22]. Therefore, for the proportion of patients with change in treatment from empirical antimicrobials to pathogen-guided treatment, we expect to be able to identify a pathogen in at least 50% of the cases using FAP *plus* versus 40% with the current standard-of-care methods.

The required sample size needed is 470 per arm (assuming a significance level of 0.025 and a power of 0.8), i.e., in total 940. Additionally, allowing for a 10% dropout rate results in a total sample size of 1045 patients. For the time to change from empirical treatment to pathogen-directed treatment, we have no data from previous studies on effect size to gauge the sample size calculation and therefore we will define the effect size in terms of the variation in the outcome (the standard deviation) as done in other studies [23].

We find it clinically relevant to be able to detect a difference of 0.2 standard deviations, e.g., if the standard deviation of the time to change is 3 days, then we can detect a difference of 0.2‧3 = 0.6 day; if the standard deviation was 5 days, we would detect a difference of 1 day. The required sample size needed is 477 per arm (assuming a significance level of 0.025 and a power of 0.8), i.e., in total 954. Additionally, allowing for a 10% dropout rate results in a total sample size of 1060 patients.

In conclusion, a sample size of 1060 will ensure that we have 80% power to detect a difference in at least one of the two primary outcomes (at a significance level of 0.05).

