### Outcomes {12}

#### Primary outcomes

There are two primary outcome variables:Provision of pathogen-directed treatment based on a microbiological test result deemed as clinically relevant within 48 h of receipt of respiratory samples. This is a binary outcome variable taking on values as follows: yes, if such treatment was given to the patient, and no, if it was not given.Time (in hours) from receipt of respiratory samples to the patient receiving pathogen-directed treatment. This is a quantitative outcome variable recording the time elapsed from receipt of respiratory samples to provision of pathogen-directed treatment based on a microbiological test result deemed as clinically relevant (as defined in the first primary outcome) or an elapse of 48 h, whichever event came first. In other words, this outcome variable is subject to right censoring at 48 h. Right censoring could potentially occur for other reasons such as no aetiology being detected or the patient dying.

Since lack of microbiological identification is a major problem in CAP patients and enhancing rapid detection of significant pathogens could have a major impact on the clinical decision-making process, we selected two correlated primary outcomes with both time to and provision of pathogen-directed treatment. Limited evidence exists to support the use of these new molecular microbiological methods over standard of care, which uses standard microbiological testing. In a retrospective study including rapid molecular diagnostics, it has been suggested that de-escalation from broad-spectrum to pathogen-directed antibiotics could be undertaken in 77% of patients with CAP, while escalation should be done in 6%; however, a RCT is needed to confirm these findings [21].

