## Statistical methods

### Statistical methods for primary and secondary outcomes {20a}

For the first primary outcome, which is a binary outcome capturing whether or not provision of pathogen-directed treatment was given, the comparison between arms will be performed using a logistic regression model. The difference between arms will be quantified by means of an odds ratio or as a difference in probabilities (“a risk difference”). For the second primary outcome, which is a quantitative outcome subject to right censoring capturing the time to pathogen-directed treatment was given, the comparison between arms will be carried out using a semi-parametric or fully parametric event-time model such as the Cox proportional hazards model or accelerated failure time model. Relevant covariate adjustment, including age and sex, will be included in both models.

Secondary outcomes will be analysed using the same two types of models as used for the two primary outcomes. However, for some quantitative secondary outcomes, there will be no right censoring present and, in such cases, linear models or linear mixed models will be fitted, depending on the absence or presence of repeated measurements.

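### The time outcome's detectable difference is illustrated with SDs of 3 and 5 days although the recorded time stops at 48 h, and its 80% power is shown for a t-test rather than the planned event-time model

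*Protocol article*

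**What the plan says.** Sample size {14} splits the significance level between the two primary outcomes: "separate sample size calculations for the two outcomes must be carried out at a significance level of 0.025 instead of 0.05". For the time outcome it reports having no earlier data on effect size and works in standardised units: "We find it clinically relevant to be able to detect a difference of 0.2 standard deviations". Two examples turn this into days: "if the standard deviation of the time to change is 3 days, then we can detect a difference of" 0.6 day, and "if the standard deviation was 5 days, we would detect a difference of 1 day". The result is: "The required sample size needed is 477 per arm (assuming a significance level of 0.025 and a power of 0.8), i.e., in total 954", which becomes 1060 after a 10% dropout allowance. No hazard ratio, time ratio or expected number of events is given for this outcome.

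Outcomes {12}, Primary outcomes, measures the time in hours from receipt of the respiratory sample and ends it at directed treatment or 48 h, whichever is first: "this outcome variable is subject to right censoring at 48 h". Statistical methods {20a} plans a "semi-parametric or fully parametric event-time model such as the Cox proportional hazards model or accelerated failure time model".

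For the binary primary outcome, Sample size {14} says "we expect to be able to identify a pathogen in at least 50% of the cases" with the panel, against 40% with standard methods, and arrives at 470 per arm. The endpoint itself is directed treatment, based on a clinically relevant result, within 48 h.

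**The concern.** The day-scale examples are the only place where the protocol tells the reader what 0.2 SD means in time. They suggest that the trial is looking for a difference of 14.4 to 24 h. On an outcome that stops at 48 h, that would be between 30% and half of the whole window, and the SDs behind it exceed anything a 0–48 h variable can have. A clinician judging whether the target effect matters would be judging the wrong quantity.

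Separately, this calculation gives the larger of the two sample sizes and so fixes the final 1060. It uses a formula for fully observed means. In a Cox or accelerated failure time analysis, precision depends largely on how many patients have the event by 48 h, and the section does not state that number.

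**Working it through.** **Inputs.** From Sample size {14}: 0.2 SD, significance level 0.025 (the figures reproduce as two-sided), power 0.80, 10% dropout, 40% vs 50%. From Primary outcomes: censoring at 48 h. From Trial design {8}: 1:1 allocation. Normal quantiles: 2.241 and 0.842, sum 3.083, square 9.505.

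**1. The protocol's own figures.**
- Time outcome, normal approximation: n = 2 × 9.505 / 0.2² = 475.3, i.e. 476 per arm. The exact two-sample t-test gives 476.5, i.e. 477 per arm and 954 in total; 954 / 0.9 = 1060. Reproduced. A one-sided 0.025 gives 393 and does not reproduce.
- With SD 3 days and difference 0.6 day, or SD 5 days and difference 1 day, the approximation gives 476 both times. The SD cancels; only the ratio 0.2 matters.
- Binary outcome, 40% vs 50%: n = (2.241 × √0.495 + 0.842 × √0.49)² / 0.1² = 469.2, i.e. 470 per arm; 940 / 0.9 = 1044.4, i.e. 1045. Reproduced. At 477 per arm, power is 80.7%.

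**2. The largest SD of the recorded time.** For a variable confined to 0–48 h, SD ≤ range / 2 = 24 h = 1 day, reached only if half the values are 0 and half are 48. Hence 0.2 SD ≤ 4.8 h. The examples' 14.4 h and 24 h are at least 14.4 / 4.8 = 3 and 24 / 4.8 = 5 times too large.

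**3. A more realistic SD (assumption: exponential times, 40% and 50% with the event by 48 h).**
- Rates per hour: −ln(0.6) / 48 = 0.01064 and −ln(0.5) / 48 = 0.01444.
- Mean time restricted to 48 h, (1 − e^(−48λ)) / λ: 37.6 h and 34.6 h, a difference of 3.0 h.
- SDs of the capped time: 15.4 h and 16.5 h, pooled 16.0 h. So 0.2 SD is 3.2 h.
- The standardised difference is 2.96 / 15.99 = 0.185. A comparison of capped means at 477 per arm would have about 73% power. This is not the planned analysis.

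**4. The planned analysis (same event proportions, proportional hazards).**
- Hazard ratio = ln(0.5) / ln(0.6) = 1.357.
- Events needed for 80% power: 4 × 9.505 / (ln 1.357)² = 408.1, i.e. 409.
- Events expected: 477 × (0.40 + 0.50) = 429.
- Power: Φ(√(429.3 / 4) × ln 1.357 − 2.241) = Φ(0.92) = about 82%.
- Hazard ratio detectable at 80% power: exp(√(38.02 / 429.3)) = 1.35.

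**5. Sensitivity to the assumed 48 h proportions (Cox, 477 per arm).**

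| Control vs panel | Hazard ratio | Events | Power |
|---|---|---|---|
| 20% vs 30% | 1.60 | 239 | 92% |
| 30% vs 40% | 1.43 | 334 | 85% |
| 40% vs 50% | 1.36 | 429 | 82% |
| 50% vs 60% | 1.32 | 525 | 83% |
| 40% vs 46% | 1.21 | 410 | 37% |
| 30% vs 36% | 1.25 | 315 | 40% |
| 20% vs 25% | 1.29 | 215 | 35% |

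A 10-point gap keeps power at or above 80% across this range; gaps of 5 to 6 points do not. All figures use 477 per arm after dropout and no covariate adjustment.

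**The case against.** Four points can be made for the protocol.

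First, the SDs are introduced as examples and do not enter the sample size. This stands in full: removing them leaves 477, 954 and 1060 untouched. A reader might infer that the trial was sized on impossible SDs; step 1 shows that it was not.

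Second, the 24 h limit applies to the recorded, capped time. Treated as a censored event time, the underlying time can run past 48 h. With the exponential times of step 3, its mean and SD would be 48 / 0.5108 = 94 h (3.9 days) and 48 / 0.6931 = 69 h (2.9 days), about 25 h apart, which is the order of the examples. So the examples are impossible only for the outcome as recorded. This reading does not rescue the calculation: a t-test on that time would need it observed in everyone, and patients without a detected aetiology may have no such time. Nor does it return 0.2 SD: the pooled SD is √((94² + 69²) / 2) = 82 h, and 25 / 82 is about 0.3.

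Third, a reader might infer that power is below 80%. The documents do not support that. With the protocol's own 40% vs 50% read as 48 h event proportions, the Cox model has about 82%. The section's conclusion claims 80% for at least one of the two outcomes, and the binary outcome alone gives 80.7% at its stated rates.

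Fourth, on the binary outcome, a reader might infer a shortfall by supposing that only 80% or 60% of identifications lead to directed treatment in each arm (40% vs 32%, power 63%; 30% vs 24%, power 44%). No section gives such rates. Plans for assessment {18a} also counts stopping treatment after negative results, so the treated proportion could exceed the identification rate, and faster results could raise it more in the panel arm. The direction of the error is unknown.

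**Conclusion.** The concern holds as a mismatch between three sections. The example SDs and detectable differences in Sample size {14} do not fit the 48 h outcome in Primary outcomes. On that outcome 0.2 SD is at most 4.8 h, whatever the distribution, and about 3.2 h under exponential times with 40–50% events. The 477 per arm is valid arithmetic for an uncensored t-test, but Statistical methods {20a} plans something else, so 80% power for the time outcome is asserted rather than demonstrated.

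No shortfall is established. About 82% power and a detectable hazard ratio of about 1.35 follow if 40% and 50% are the 48 h event proportions and hazards are proportional; both are assumptions. The 50% vs 40% are identification rates standing in for treatment rates, which leaves both outcomes' power uncertain in either direction. This is a correction to stated figures for a primary outcome; it does not show that the trial is too small.

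**What to change.** In Sample size {14}:

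- Delete the 3- and 5-day examples.
- State the time outcome's effect on the scale to be analysed: a hazard or time ratio with the expected number of events by 48 h (for example, about 429 events and a detectable hazard ratio of about 1.35 under the stated assumptions), or a difference in mean time restricted to 48 h, in hours, with an SD no larger than 24 h.
- Say that 50% vs 40% are pathogen-identification rates used as a proxy for the proportion given directed treatment within 48 h, and give power over a range of such proportions, both above and below. The 104-patient feasibility cohort, in which every lower respiratory sample was tested by both methods, may help to set that range.

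The cost is one rewritten paragraph. The sample size stays at 1060, and no endpoint, analysis or procedure changes. The stated target effect becomes a few hours instead of 0.6 to 1 day, and some scenarios in the power range will fall below 80%.

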### Recruitment {15}

The number of CAP patients admitted to Bergen Hospital Trust, including the emergency department at HUH, from March 2020 to March 2021 was approximately 1200 [24]. By including suspected CAP patients Monday until Friday between 8 am and 9 pm, we expect to be able to recruit ~350 CAP patients per year. Therefore, enrolment is expected to be completed within the 3-year period: 2020–2023.

## Assignment of interventions: allocation

### Sequence generation {16a}

The allocation sequence is computer-generated using the extension package “blockrand” within the statistical environment R (version 3.6.3; Vienna, Austria) with a pre-specified seed number for initiating the random number generator in R. Specifically, blocked randomised is applied with blocks with 4, 6 or 8 patients; the block sizes will occur in random order to ensure approximately equal allocation over the year.

### Concealment mechanism {16b}

The generated allocation sequence is prepared and entered in the eCRF (Viedoc) by staff not involved in the trial. It remains concealed until the moment the patient is randomised, which happens once the Department of Microbiology at HUH receives the respiratory tract sample.

### Implementation {16c}

The patients are included at the emergency department by study nurses and study physicians. When the Department of Microbiology receives the respiratory tract specimen, a bioengineer initiates the randomised process that is implemented in Viedoc. The result of the allocation is made available for the staff at the Department of Microbiology in the laboratory’s electronic data system and guides the processing of the lower respiratory tract samples into one of the arms.

### Assignment of interventions: blinding

### Who will be blinded {17a}

CAP patients are blinded for the intervention, and medical staff in the emergency department are blinded at patient inclusion and hence have no influence on allocation which is assigned at the Department of Microbiology, HUH. Owing to the nature of the intervention, research staff and clinical care providers are not blinded to group allocation. Furthermore, data managers, outcome assessors and statisticians are not blinded. However, in contrast to data managers and outcome assessors, the involved statisticians do not have any direct access to data, which are stored within the Viedoc platform for patient registry at HUH.

### Procedure for unblinding if needed {17b}

Not applicable. Our intervention in the FAP *plus* arm involves microbiological diagnostic testing only. Furthermore, the allocation will be visible in the patient case record in the intervention group when the result of the FAP *plus* are available, normally within 1–2 h.

## Data collection and management

### Plans for assessment and collection of outcomes {18a}

Baseline information is collected by study nurses or investigating physicians through a structured interview in the emergency department. Symptoms and findings upon clinical examinations are recorded. Data pertaining to antimicrobial treatment and decisions, results from laboratory tests and medical imaging are obtained from electronic medical records and charts, after patient discharge, and used for the evaluation of the primary outcomes. For each patient, two experienced physicians separately evaluate the clinical relevance of all microbiological findings [19] and determine if and when the patient received pathogen-directed antimicrobial treatment based on a microbiological test result. In case of any inconsistency between the two physicians, a third independent physician will arbitrate. To be considered as pathogen-directed treatment, study physicians will note if (a) there is a change in antimicrobial treatment based on a microbiology test result or (b) a continuation of already correctly initiated antimicrobial treatment based on a microbiology test result, and (c) discontinuation of antimicrobial treatment based on negative microbiological test result(s). Empirical and pathogen-directed therapy will be determined using national guidelines recommended by the Norwegian Directorate of Health, data from national susceptibility reports, as well as results from anti-microbial susceptibility testing provided by the Department of Microbiology, HUH, as appropriate [25, 26]. Data will be registered in our eCRF (Viedoc). Data for the 30- and 90-day mortality, and 1- and 5-year mortality will be obtained from the Norwegian Cause of Death Registry.

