#### The standard-of-care arm

The comparator arm corresponds to standard-of-care diagnostics currently provided to CAP patients at HUH. As described [19], this includes bacterial culture of respiratory tract samples and blood according to current guidelines (adapted from [20]). Blood culture isolates and relevant respiratory isolates are identified with matrix-assisted laser desorption/ionization time-of-flight mass spectrometry (MALDI-ToF MS) using the Bruker’s microflex LT instrument, MBT Compass software ver. 4.1 and Compass Library DB-8468 (Bruker Daltonics, MA, USA). Nasopharyngeal and/or oropharyngeal swabs are examined by an in-house real-time PCR test to detect respiratory viruses and atypical bacteria (influenza A and B, human parainfluenza viruses 1-3, respiratory syncytial virus, human metapneumovirus, rhinovirus, SARS-CoV-2, *Bordetella pertussis*, *Bordetella parapertussis*, *Mycoplasma pneumoniae* and *Chlamydia pneumoniae*). The total turn-around time for the in-house PCR test is up to 48 h and is comparable to other centres nationally. Standard methods also include the pneumococcal urine antigen test (Quidel Corporation, San Diego, USA). Any additional tests requested by the treating physician are noted and counted as part of standard methods. A positive SARS-CoV-2 result, growth in blood cultures and positive pneumococcal antigen test results are phoned to the treating staff.

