#### *The FAP* plus *arm*

The FAP *plus* arm entails extended and rapid diagnostics on lower respiratory tract samples and telephonic feedback to treating staff with results. The feedback does not involve advice on treatment. All patients will receive the standard microbiological tests described above, with additional testing by the FAP *plus*. Through a feedback loop, both negative and positive FAP *plus* results are telephonically communicated to the treating staff.

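### Stopping antimicrobials on a negative result counts as a primary event in the adjudication rule, but the outcome definition, censoring text and planning rates do not reflect it

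*Protocol article*

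**What the plan says.** The Primary outcomes section defines the first outcome as "Provision of pathogen-directed treatment based on a microbiological test result deemed as clinically relevant within 48 h of receipt of respiratory samples", coded "yes, if such treatment was given to the patient, and no, if it was not given". The second is the time to that event, censored at 48 h, with the remark "Right censoring could potentially occur for other reasons such as no aetiology being detected or the patient dying".

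Section {18a} gives the working rule. Two physicians, with a third to arbitrate, "determine if and when the patient received pathogen-directed antimicrobial treatment based on a microbiological test result". One adjudication therefore supplies both the yes/no outcome and the event time. Three criteria are listed: (a) a change of treatment on a test result, (b) continuing treatment that was already correct on a test result, and "c) discontinuation of antimicrobial treatment based on negative microbiological test result(s".

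Sample size {14} plans the first outcome on this basis: "we expect to be able to identify a pathogen in at least 50% of the cases using FAP *plus* versus 40" per cent under standard of care.

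On reporting, in the FAP plus arm "both negative and positive FAP *plus* results are telephonically communicated", and Procedure for unblinding {17b} says these results are normally available within 1–2 h. For standard of care the protocol states: "A positive SARS-CoV-2 result, growth in blood cultures and positive pneumococcal antigen test results are phoned to the treating staff". The in-house PCR there takes up to 48 h.

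**The concern.** Take a patient in whom no pathogen is found and whose antimicrobials are stopped at 6 h because of a negative result. Under criterion (c) this is a primary event at 6 h. Under the Primary outcomes section the same patient belongs to the group cited as a possible reason for censoring, and nothing there tells the reader that stopping without a pathogen counts as treatment having been given. The planning rates describe a third quantity, the share with a pathogen identified.

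What is at stake is the meaning of the primary result. If (c) events are a material share, a difference between arms may reflect faster stopping, better treatment of identified pathogens, or both, and the primary analysis cannot tell them apart. A stewardship gain from stopping may be worthwhile, but it is a different claim from the one the outcome's name makes. The assumed event rates, and hence the power, also no longer refer to the event being adjudicated.

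**Working it through.** **1. The plan's own figures.** Inputs from Sample size {14}: 50% versus 40%, alpha 0.025 (taken as two-sided), power 0.80. With the pooled two-proportion formula,

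n = [2.2414 × √(2 × 0.45 × 0.55) + 0.8416 × √(0.24 + 0.25)]² / 0.10² = 469.2, so 470 per arm, as stated.

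Total 940; 940/0.9 gives 1045. The second outcome's 477 per arm is reproduced by an exact t-test calculation at 0.2 SD; 954/0.9 = 1060. The arithmetic is sound. At 477 per arm, 50% versus 40% has power 81%.

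**2. What criterion (c) adds.** Let d be the share with a pathogen identified and q the share of the remainder stopped on a negative result within 48 h. Following the plan, every identified pathogen is treated as an event. The event rate is then

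d + (1 − d) × q.

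The protocol gives no value for q in either arm, so **every q below is an assumption**. Power is for 477 per arm, two-sided alpha 0.025.

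**3. Planned detection (50% versus 40%).** With the same q in both arms the difference is (0.50 + 0.50q) − (0.40 + 0.60q) = 0.10 × (1 − q), so equal stopping always shrinks it.

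| q FAP plus / standard | Event rates | Difference | Power |
|---|---|---|---|
| 0 / 0 | 50% v 40% | 10 points | 81% |
| 10% / 10% | 55% v 46% | 9 points | 71% (586 per arm for 80%) |
| 20% / 20% | 60% v 52% | 8 points | 60% (731 per arm for 80%) |
| 10% / 0 | 55% v 40% | 15 points | 99% |
| 10% / 20% | 55% v 52% | 3 points | 10% |

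**4. No gain in detection (40% in both arms).** The difference is 0.60 × (q FAP plus − q standard) and comes wholly from stops.

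| q FAP plus / standard | Event rates | Chance of significance |
|---|---|---|
| 5% / 0 | 43% v 40% | 10% |
| 10% / 2% | 46.0% v 41.2% | 23% |
| 10% / 0 | 46% v 40% | 36% |
| 20% / 10% | 52% v 46% | 35% |
| 20% / 0 | 52% v 40% | 93% |

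**5. The time outcome.** The same adjudication sets the event time, so (c) enters there too. The protocol gives no time distribution, and I have not put a figure on it.

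**The case against.** A reader might infer a flat contradiction. The text does not go that far. The outcome definition requires a clinically relevant test result, not a positive one, and the censoring remark says only that censoring could occur. The sections can be read together: a no-aetiology patient whose antimicrobials continue is censored, and one stopped on a negative result is an event. That reading is possible, but the protocol does not state it, the wording about treatment being given fits (c) poorly, and the planning rates still exclude such events.

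A reader might also infer that (c) favours the FAP plus arm. The fast, phoned negative results make it plausible that (c) is reached earlier or more often there. But (c) needs only a negative result or results, not a complete negative work-up, so a control patient can meet it on a negative antigen test, culture or PCR. Listing which results are phoned does not say that negatives go unreported, and 48 h is the PCR's upper limit. Faster negatives are also part of the intervention, so an effect through them is not in itself bias.

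Finally, the protocol has partial safeguards: subgroup analyses by aetiology, including unknown aetiology, and secondary outcomes for detected aetiology, single-dose treatment and antibiotics for at most 48 h. They would give hints, but none isolates stops made because of a negative result.

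**Conclusion.** The point stands as a mismatch between three sections. The adjudication rule admits stops on negative results, the outcome and censoring text does not say so, and the 50% and 40% leave them out. A difference in either primary outcome could therefore arise partly without any pathogen being found.

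The documents fix neither direction nor size. On the assumed rates, equal stopping of 10% to 20% lowers power for the binary outcome from 81% to 71% or 60%. With no detection gain, unequal stopping gives a chance of significance from 10% (5% versus 0) to 93% (20% versus 0, the extreme of the range). These figures rest on the assumed q and on every identified pathogen becoming an event.

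Two stronger conclusions are not supported. The protocol does not show that the FAP plus arm is favoured. Nor does it follow that (c) must be dropped: redefining both primary outcomes with 354 patients enrolled by February 2022, and with assessors who know the allocation, carries its own risk.

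**What to change.** - In the Primary outcomes section, state whether a patient with no pathogen found who is stopped on a negative result is an event or is censored, and bring {18a} and the censoring remark into line with that.
- In Sample size {14}, state that the 50% and 40% exclude such events.
- Flag each adjudicated event by criterion (a), (b) or (c). Where (c) comes first, also record the first (a) or (b) event within 48 h, so that the analysis without (c) can be run.
- Report discontinuation on negative results within 48 h of sample receipt as a separate binary secondary outcome.
- Report both primary outcomes with and without (c). Without (c), a patient whose only event is (c) is a no for the first outcome and is not an event for the second. Attribute a benefit to treatment directed at an identified pathogen only if it holds without (c).

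The cost is one adjudication flag and one extra analysis per primary outcome, and the primary definition can stay as it is. The adjudication form is not shown. If it does not already hold the criterion, patients already assessed would need the flag added from their records.
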